### Secondary Objectives

To determine the efficacy of each intervention in modifying the following CVD risk factors: smoking status, fruit and vegetable intake, alcohol consumption, fasting and 2-hour post-challenge plasma glucose, fructosamine, waist circumference, weight, BMI, total cholesterol, HDL cholesterol, LDL cholesterol and triglycerides, systolic and diastolic blood pressure, estimated 10-year CVD risk, estimated risk of diabetes and body fat percentage.

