**Figure 1 F1:**
[figure not shown]

Physical activity, clinical and psychological information will be collected before randomisation and one month after delivery of the intervention. A personalised CVD risk estimate and lifestyle advice will be provided to all participants at the end of 4 weeks making it a waiting-list control design. The inclusion of a control group receiving neither a risk estimate or lifestyle advice but undergoing baseline and follow up measurement will control for Hawthorne effects[19].

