### Outcome assessment

Follow-up at four weeks occurs for all measures including oral glucose tolerance test, blood samples, anthropometric measurements, smoking status, current medication, alcohol intake and questionnaires with the addition of a recall of risk information questionnaire. Physical activity is again measured by accelerometer for seven days in the week before the second study visit.

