### Sample size and rate of recruitment

The study has 80% power at the 5% level of significance to detect a difference of 30,000 total accelerometer counts per day of physical activity between the groups with a sample size of 46 per cell, assuming the estimated total counts per day is mean (SD) 275,400 (101,600) minutes[31]. This equates to 92 participants per arm of the study. We will randomise a total of 200 subjects to allow for a small drop-out rate. We expect retention of study participants to be high because of the short duration and non-invasiveness of the study. Recruitment is anticipated to continue for one year.

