### Statistical analysis

Only data for participants who record at least 500 min/day of activity for at least 4 days during each 7 day period will be analysed. Data will be presented in terms of total body movement (counts·day^-1^), which is an indicator of the total volume of physical activity, and time (minutes·day^-1^) spent at different activity intensity categories averaged per day over the measurement period. Intensity thresholds for sedentary, light, moderate, vigorous and very vigorous intensity physical activity will be defined according to Freedson *et al *and Ekelund *et al*[32,33]. We will also determine the average number of 5- and 10-min bouts of sustained physical activity at moderate or greater intensity allowing 1 min to drop below the threshold for moderate activity in each 5-min bout. We will calculate the proportion of participants in each group accumulating 30 min or more per day of moderate or greater intensity physical activity, the current UK recommendation for physical activity[28]. Data reduction, cleaning, and analyses of accelerometer data will be performed using appropriate software (MAHUffe; see ). Generalized linear model (Poisson distribution or Negative Binomial distribution) as appropriate will be used and estimates of Rate Ratios along with 95% confidence interval will be presented.

Demographic, clinical and biochemical study variables will be summarized using number (percentage) and measures of location and dispersion as appropriate. The change in the study parameters from baseline to one month will be analysed and inference drawn using appropriate statistical methods, keeping in mind the nature of distributions of the study variables. Analysis will be by intention to treat (ITT).

To analyse the highly skewed EQ-5D scores, appropriate non-parametric technique will be used. Other questionnaire data will be analysed using appropriate non-parametric tests to compare average scores as well as distribution of scores in each group. Should a questionnaire generate only a finite number of scores, the data will then be considered polytomous and suitable statistical techniques will be used to analyse any such data.

Any missing biochemical data will be imputed using the Last Observation Carried Forward technique. Any missing accelerometer data however, will not be imputed for.

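### With only two measurement times, LOCF for biochemical outcomes is baseline carried forward: each missing four-week value enters the analysis as a change of exactly zero

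*Protocol article*

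**What the plan says.** The rule is in the protocol article, Statistical analysis: "Any missing biochemical data will be imputed using the Last Observation Carried Forward technique". The next sentence exempts the primary outcome: "Any missing accelerometer data however, will not be imputed for". The same section names the quantity to be analysed, "The change in the study parameters from baseline to one month will be analysed", and commits to intention to treat.

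The measurement schedule is in two places. The text below Figure 1 in Study Design says: "Physical activity, clinical and psychological information will be collected before randomisation and one month after delivery of the intervention". Outcome assessment says: "Follow-up at four weeks occurs for all measures including oral glucose tolerance test, blood samples". No visit between the two is described.

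The biochemical measures among the Secondary Objectives are glucose (fasting and 2-hour), fructosamine and the lipids. Serum cotinine and plasma vitamin C appear as additional outcomes in the Abstract and are drawn at baseline. The Discussion justifies them as objective measures of smoking and of fruit and vegetable intake.

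No dropout rate is stated. Sample size and rate of recruitment asks for 46 per cell, plans to randomise 200 to cover a small loss, and expects high retention.

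**The concern.** LOCF is usually discussed for trials with several follow-up visits, where the carried value is at least post-randomisation. Here the last observation before a missing four-week value is always the baseline value. The analysed quantity is change from baseline, so the rule inserts a change of zero, without error, for everyone who does not return.

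Three things follow if dropouts would have changed as completers did:

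- A real effect is diluted.
- The standard error shrinks, because the imputed zeros raise the apparent sample size and add no spread.
- If loss differs between arms while all participants drift in the same direction, the rule produces a difference that no intervention caused.

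A common drift is plausible here, since Study Design includes a control group precisely to allow for an effect of being measured. The trial is also described as a pilot for a larger one, and the SD of change is a quantity that a larger trial would take from it. LOCF understates that SD as well.

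**Working it through.** **Inputs from the document.** Two measurement times; change from baseline analysed; 46 × 4 = 184 needed; 200 randomised. Implied loss: 1 − 184/200 = 0.08, and 184/0.92 = 200, so the inflation is consistent with 8%. This rate is inferred, not stated.

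**Inputs assumed.** Dropouts would have changed as completers did. For the simulation: outcome SD 1, baseline-to-follow-up correlation 0.7, 100 per arm (one side of a factorial comparison with 200 randomised), loss at random within arm, 6,000 simulated trials per scenario.

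**Effect estimate.** Let the true mean changes be μ₁ and μ₀, and let a fraction m be lost in each arm. The LOCF mean in each arm is (1−m)μ + m·0, so the estimated difference is (1−m)(μ₁ − μ₀). At m = 0.08 it is 0.92 of the truth.

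**Standard error.** With SD of change σ, the variance of change after LOCF is (1−m)σ² + m(1−m)μ², spread over n rather than n(1−m). For one arm, the ratio to the complete-case standard error is

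(1−m) × √(1 + mμ²/σ²).

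For μ small relative to σ this is about 1−m, or 0.92 at 8%. If the mean change were as large as its SD, it would be 0.92 × √1.08 = 0.956. The SD of change itself falls by √0.92 = 0.959, about 4%.

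**Simulation, change-score analysis, equal loss.**

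| Loss | True effect (SD) | Complete-case estimate, SE, coverage | LOCF estimate, SE, coverage |
|---|---|---|---|
| 8% | 0 | −0.001, 0.1139, 95.3% | −0.001, 0.1048, 95.3% |
| 8% | 0.30 | 0.300, 0.1140, 95.2% | 0.276, 0.1052, 94.3% |
| 20% (assumed) | 0.30 | 0.300, 0.1225, 94.8% | 0.240, 0.0987, 90.9% |
| 20% (assumed) | 0.50 | 0.499, 0.1224, 94.9% | 0.399, 0.0998, 82.5% |

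Estimate and standard error shrink together. At 8% and a true effect of 0.30, the ratio is 0.2996/0.1140 = 2.63 for complete cases and 0.2755/0.1052 = 2.62 for LOCF; power is 74.4% against 74.1%. With no true effect, both reject in 4.7% of trials. The lost coverage therefore comes from an interval that is both shifted towards zero and too short, not from a distorted test.

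Adjusting the LOCF data for baseline does not repair this. At 8% and 0.30, ANCOVA gives 0.275 with 94.4% coverage; at 20% and 0.50 it gives 0.400 with 81.1%.

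**Unequal loss.** With no true effect, a common change c, and losses m₁ and m₀, LOCF gives (1−m₁)c − (1−m₀)c = (m₀ − m₁)c.

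- Assumed 4% v 12%, c = −0.3 SD: 0.08 × (−0.3) = −0.024 SD. Simulation gives −0.025 (complete cases about 0), roughly a quarter of the standard error of 0.1055; rejection rises to 5.5%.
- Assumed 5% v 15%: a spurious difference of 0.10c in size.

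**The case against.** The strongest defence is that people who do not return to a behaviour-change study may well not have changed. On that view zero is a fair value, complete-case analysis overstates the effect among all randomised, and the rule suits the intention-to-treat commitment. Part of this stands: the (1−m) dilution is a bias only if dropouts would have changed as completers did, and the document cannot settle that. It does not rescue the rule as the main analysis. The precision gained comes from the assumption and not from data: at 8% loss the standard error is about √0.92 = 0.959 of what full follow-up of all 200 would give. Nor is the rule reliably cautious, because unequal loss with a shared trend can move the result in either direction.

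It is also fair to say that the only confidence interval the section specifies is for accelerometer rate ratios. The point about precision therefore applies to whatever standard errors or intervals are reported for the biochemical changes.

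A reader might infer more than the document supports:

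- **That the primary analysis is affected.** It is not; accelerometer data are expressly left unimputed.
- **That the tests are invalid.** Under equal random loss, type I error and power barely change.
- **That 8% is a planned rate, or that 15% or 20% loss is expected.** The first is inferred from 184 and 200; the others are illustrations.
- **That missing baseline values are a practical gap.** LOCF cannot fill them, but Baseline assessment places data collection before randomisation, so they should be rare. No weight is put on this.

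**Conclusion.** The point holds for the secondary and additional biochemical outcomes. The stated rule, applied to the stated schedule, imputes zero change and counts it as observed. This is an objection to a method that the article fixes, not to detail left for an analysis plan.

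At the implied 8% loss, equal between arms, the harm is modest: estimate and standard error each about 8% too small, and coverage about 94% for a true effect of 0.30 SD. At an assumed 20% loss, coverage falls to 90.9% for that effect and 82.5% for an effect of 0.50 SD. Unequal loss adds a spurious difference equal in size to the common change times the difference in loss.

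These sizes assume that dropouts would have changed as completers did and, for the standard error, that mean change is small relative to its SD. The change is worth making before analysis because the alternative is nearly free, but it does not threaten the trial's main conclusion.

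**What to change.** Remove LOCF as the main approach for biochemical outcomes. Replace it with one of:

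- a baseline-adjusted analysis (ANCOVA) of the observed four-week values with both factors in the model, on a transformed or otherwise suitable scale for skewed markers such as cotinine and triglycerides; this is valid if values are missing at random given baseline and allocation; or
- multiple imputation of missing four-week values from baseline and both factors.

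If the assumption that non-returners did not change is of interest, keep baseline carried forward as a sensitivity analysis under that name, and report the number of imputed values by arm.

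The cost is a change of wording, slight extra programming (somewhat more for multiple imputation), and slightly wider intervals on secondary outcomes: about 1/0.92 = 1.09 times the LOCF width at 8% loss. No change to data collection or trial conduct is needed, and the primary analysis is untouched.

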### Publication of results

It is anticipated that the results of the study will be published towards the end of 2009.

## Discussion

The aim of this study is to evaluate whether provision of personalised 10-year CVD risk estimates can increase intention to change behaviour and increase physical activity in individuals at high risk of CVD. The simultaneous randomisation to a risk estimate or not and to a lifestyle advice intervention or not will allow us to determine whether 10-year CVD risk information can increase intention to change behaviour and also if a brief lifestyle advice intervention can increase intention to change behaviour. The evidence that increased physical activity can reduce CVD is well established but our study represents a novel approach at trying to increase physical activity in a high risk group.

The outcome measures used have been chosen to provide objective measures of behaviour without undue inconvenience to participants. Accelerometers have been chosen as a measure of physical activity because they allow measurement of free living physical activity, avoid the need for whole-room calorimetry and are more accurate than the completion of physical activity questionnaires. 100,000 accelerometer counts are approximately equivalent to 30 minutes of brisk walking in a person of average size. In the MRC PROACTIVE trial, a behavioural intervention to promote physical activity among the 20–50 year old offspring of people with type 2 diabetes, the cohort exhibited a 10,000 increase in total counts per day between baseline (mean counts per day 264,000) and follow-up at one year (mean counts per day 274,000)[31]. Plasma vitamin C provides a robust measure of fruit and vegetable intake and has been shown to be inversely related to mortality from cardiovascular disease and ischaemic heart disease in men and women[34]. Serum cotinine is a reliable objective indicator of the quantity of tobacco smoked [35].

The Illness Perception Questionnaire has been included to provide insight into the influence of self-regulation on the decision to adhere to medical advice [36].

The study also includes measurements of potential mediators and moderators. Personality traits in particular optimism and pessimism (future orientation), are known to influence response to health information[37] this is measured by questionnaire[38] in order to examine its effect on the results of the study. Deprivation and a feeling of being unsafe in a community have been shown to be associated with lower rates of physical activity[29]. We collect age at leaving school and electoral ward as surrogate measures of deprivation. In order to investigate the impact of considering oneself already active on the results of the study we are using a recent physical activity questionnaire[39]. An adapted Lerman Cancer Worry Scale is being used to assess the impact of CVD risk information on worry about diabetes[22] although work in the field of pre-natal genetic screening suggests that numerical risk information can be successfully communicated to individuals and increase awareness of risk without raising anxiety[40].

Studies to investigate the use of personalised risk information are needed across a wide range of clinical topics to explore the impact of individualised risk estimates on knowledge, attitude, behaviour and patient understanding[41] with the aim of demonstrating a link between informed decision making and behaviour change[42]. We hope to demonstrate proof of principal that personalised risk information and brief theory-based advice can provide motivation to initiate behaviour change and to examine the intermediate measures that link changing beliefs to subsequent behaviour change. We have included a robust measure of physical activity and our intervention focuses on increasing activity as part of day to day life, factors that have limited the interpretation and applicability of other studies[13].

This project, if successful, has a high probability of providing generalisable results. Personalised risk scores can readily be assessed in many clinical situations and the intervention tested could be used in almost all individuals without modification.

